**Inclusion criteria:**
Patients with a history of paroxysmal, persistent, or permanent atrial fibrillationAccess to an internet connection and adequate equipmentMastery of the country’s first languageInformed consent provided by the participant
**Exclusion criteria:**
Organic or symptomatic mental disordersAlzheimer diseaseMental and behavioral disorders due to alcohol abuseMental and behavioral disorders due to drug abuseRefusal of patients to receive basic drug therapy

### Intervention Cohorts

The full pilot arm of the study will be conducted multinationally in Greece, Ukraine, and Kazakhstan (Figure 1). In Greece, a pool of 700 patients will be reached by phone, and they will participate in the trial from their home. From among the patients contacted remotely, and from those who respond, those who would be eligible will be asked to complete the intervention. From among the patients who choose to complete the quiz, half of them will be randomly allocated to the control (normal clinical information) cohort, while the other half will be informed with the help of VP vignettes. In Ukraine, 160 patients will be reached and will be divided into the control and intervention groups. Finally, at the Kazakhstan center, 190 patients will be contacted.

Given that all recruitment and adherence criteria are followed, sufficient sample sizes for control and intervention groups will be ensured so as to use the Welch *t* test for analysis, which is robust to large sample size inequalities, in order to not exclude any useful data from the generalized multicenter VP cohort.

**Figure 1 figure1:**
[figure not shown]
The flowchart of the full pilot arm of the study. VP: virtual patient.

### Blinding (Masking)

Participants and trial personnel will not be blinded after the point of assignment to interventions because of the nature of the interventions and outcomes assessed. Participants will know which group they will belong to because the group-specific intervention will follow immediately after randomization.

### The Intervention

The 2 groups that will be compared are as follows.

#### The VP Cohort

In this cohort, doctors of the research team will contact patients and ask them to participate in the VP vignette case (see *The VPs* section for a detailed description of the virtual scenarios used in the intervention, and the *The Technical Architecture of the Mobile App* section for details of the mobile app that will be used for delivering the intervention). At the end of the case questions, further information will be provided.

#### The Control (Normal Clinical Information) Cohort

In this cohort, doctors of the research team will contact patients and provide the protocol—this will include dictated information for patients with AF.

### The Technical Architecture of the Mobile App

A mobile VP player app has been created, which is capable of tracking the following user data: a detailed log of pathway detection and tracking, time spent in each node of the VPs or mobile VP, tracking of milestones, rate of successful completion of the VPs or mobile VP, and connection to learning outcomes. The player follows a flat development approach and should be available as a progressive web application. A progressive web application is a type of web-based application software that is built using standard web technologies such as HTML, CSS, and JavaScript. It is aimed to be compatible with any platform that supports a standards-compliant browser. The ability to work offline, receive push notifications, and access device hardware will enable the creation of user experiences similar to those found in native applications on desktop and mobile devices. Because a progressive web application is a subset of a web page or website known to be a web application, neither developers nor users should be required to install web applications through digital distribution systems such as the Apple App Store or Google Play.

Technically, communication between the backend and the front end player is accomplished through the use of the JSON application programming interface standard [27], which is an extremely efficient method of exchanging data over slow networks (eg, mobile phone networks).

The system's appearance and feel are based on Bootstrap, a free and open-source CSS framework for developing responsive, mobile-first front end web applications. It would be optimized for smartphone screens so as to provide a “mobile-first” user experience.

### The VPs

Three scenarios will be explored by the participating medical teams. All will be focused on the patients, since these are the target group of the VPs. A tabulated outline of these scenarios is presented in Table 1. The first scenario should be dealing with a chronic case of AF, including guidance for good medication adherence, systematic medical appointments, and correct communication. The second scenario would be about detecting early onset and prevention of paroxysmic AF. The third scenario will deal with a case of AF that involves lifestyle-compounding factors to the disease (smoking, drinking, and unhealthy eating), as well as more heavy complications that are significantly more probable in such cases.

**Table 1 table1:** Outline of suggested scenarios and educational objectives of virtual patients.

Scenario theme	Educational objectives (after encountering this educational virtual scenario vignette, the patient will be able to…)
Chronic case of AF^a^	Identify correct medication adherence practices Identify the correct frequency regimen of doctors’ appointments Identify correct dietary restrictions
Early-onset and paroxysmic AF	Identify initial onset of symptoms of AF Identify timely medical consultation practices Recognize the correct medicinal adherence procedure for the condition Identify the correct exercise intensity to manage the condition
AF with lifestyle- compounding factors to the disease (smoking, drinking, and unhealthy eating)	All educational objectives of “Chronic case of AF” Identify risks of high-impact complications Identify best practices for recovering from missed doses of medical treatment

^a^AF: atrial fibrillation.

Iterative brainstorming between the medical experts of all study centers will produce the detailed VP scenarios in the mobile digital platform (for details, refer to the previous section, *The Technical Architecture of the Mobile App*). After an internal review of these scenarios by the multinational expert panel, a selection would be made for the final case to be used. In that context, the team will choose to simply use 1 scenario in the multicenter multinational cohort trials. The most appropriate scenario would have the following characteristics: (1) it should be the most relevant—a significantly larger proportion of patients should be targeted; (2) it should be the most clinically impactful—it is important and useful for patients with AF to be aware of AF complications; and (3) it should be the most educationally important—both patients who fall within the parameters of the described case and those who do not would benefit from information and preventative knowledge of the impact of AF.

An acceptance rate of 75% by medical experts for each criterion for each scenario should be reached to be eligible for recruitment. Moreover, this patient education intervention will be based on techniques from the behavior change technique taxonomy—an international consensus for the reporting of behavior change interventions [28].

After this selection, a process of localization and adaptation to the specifics of each center (Greece, Ukraine, and Kazakhstan) would be conducted.

### Evaluation Design

#### Evaluation Instruments

For educational efficacy, a multiple-choice questionnaire (MCQ) for knowledge retention will be used (Textbox 2). The choice of questions was based on the European Society of Cardiology’s *Guidelines for Management of Atrial Fibrillation* [29]. This instrument will be translated for all participating centers in Greece, Ukraine, and Kazakhstan. The translation and evaluation of the translation will be performed by teams of bilingual experts. The instrument in its original version will be provided to bilingual persons in alternating language order and will be assessed accordingly. Scoring each questionnaire follows a simple process of allocating a numerical score equal to the number of choices in the MCQ to weigh each response for randomly selecting the correct question. For example, a question that has 4 possible responses in the MCQ will be scored 4 points if answered correctly, while a question that has 5 possible answers will be scored with 5 points if correctly answered.

Questionnaire for knowledge retention on atrial fibrillation (the asterisk indicates the correct answer).
**1. Atrial fibrillation:**
Is the most common cardiac arrhythmiaMore often concerns older people, but can occur in any ageMay be related with thyroid disordersAll of the above*
**2. The most common symptom of atrial fibrillation is:**
Chest painPalpitations*DizzinessBlurry vision
**3. How can atrial fibrillation be diagnosed?**
Following an electrocardiogram evaluated by a cardiologist*By describing symptoms of the arrhythmia to the doctorBy checking the indication ‘’arrhythmia’’ of the blood pressure deviceAll of the above
**4. What is the most important complication a patient with atrial fibrillation not receiving treatment may suffer?**
Fainting spellsMyocardial infarctionLethal arrhythmiaIschemic stroke*

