**5. Treatment with oral anticoagulants always mandates frequent blood tests:**
TrueFalse*

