**10. A patient that is under warfarin:**
Cannot switch to a newer oral anticoagulant if he/she has good anticoagulation control (international normalized ratio within the desired range)Can follow an unrestricted dietCan get advice from his doctor regarding treatment with a newer anticoagulant, so as there is no need for frequent blood tests*Always has good anticoagulation control (INR within the desired range) if he/she receives his medication in a fixed dose

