## Results

The trials will start in 2024 and are expected to end later that year or in early 2025 or when the needed sample size is achieved. The initial results are expected by March 2024.

To assess the results from the prepilot evaluation questionnaires, the Welch *t* test will be conducted. Of note, we decided to conduct the Welch *t* test because some of our sample sizes will be heavily unequal between intervention and control groups. The standard Student *t* test is robust to inhomogeneity of variance when sample sizes between cohorts are the same; however, this is not true for largely differing cohort sample sizes. The Welch *t* test does not assume homogeneity of variance and, hence, is robust to widely varying sample sizes [30,31].

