## Discussion

### Expected Findings

The results of this study aim to demonstrate the efficacy of the VP educational modality in transferring knowledge in an impactful way so that it would be useful and retained by the learner. The rationale for this kind of expected efficacy may be attributed to various factors. The impact of information passed through narrative vehicles has been identified early on [32]. Additionally, the initiative that the learner has to guide the narrative through their choices facilitates engagement through 2 avenues: one avenue is the agency that the learner has over their narrative exploration, and the second one, dependent on the first but not identical, is the ability to direct the narrative toward educational needs that the learner may have. These factors are compounded by the immediacy and ease of access that the mobile delivery platform offers, which can create an engaging and user-friendly experience that may amplify the educational impact.

This work will focus on knowledge retention and efficacy and not on perceived changes in quality of life. The impact of AF itself in the quality of life of patients is well documented with a validated questionnaire that has been available since the last decade [33]. A cursory search with the keyword “AFEQT” revealed more than 550 references on Google Scholar, including several reviews (for characteristic examples, see Kotecha et al [34] and Parameswaran et al [35]).

On the other hand, there is a significant body of literature that has identified the perceived impact of impactful patient education in their risks for serious complications and quality of life. AF, when first diagnosed, is an overwhelming situation for the patient, and reliable information is one of the first requirements for alleviating the initial possible shock [36,37]. Furthermore, lack of knowledge leads patients with AF to have significantly skewed perceptions about the importance of their condition and the true risks that stem from this potentially life-threatening, possibly chronic, condition.

Multiple studies have demonstrated that patients do not identify the possibility of stroke as an acute complication of AF; a lot of them cannot even identify their arrhythmias as AF, and they do not recognize AF as life-threatening even though they receive verbal or printed information about their condition [38,39].

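### Later quiz items cue the answers to items 4 and 5, which may modestly dilute the VP–control difference if patients can look ahead, go back or retake the quiz

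*Protocol article*

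**What the plan says.** Under Evaluation Instruments the Protocol article states: "For educational efficacy, a multiple-choice questionnaire (MCQ) for knowledge retention will be used". No other efficacy instrument is named, and efficacy is one of the primary outcomes listed under Study Design. A correct answer earns as many points as the item has options: "a question that has 4 possible responses in the MCQ will be scored 4 points if answered correctly".

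The items that matter in Textbox 2 are:

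- **Item 4:** "What is the most important complication a patient with atrial fibrillation not receiving treatment may suffer". The key is ischemic stroke. The wrong options are fainting, myocardial infarction and lethal arrhythmia.
- **Item 5 (true/false):** "Treatment with oral anticoagulants always mandates frequent blood tests". The key is false.
- **Items 6 to 9:** each mentions stroke as something anticoagulation prevents or as a danger that treatment bears on. In items 6 and 7 the mention is in a wrong option. In item 8 it is in one of the true options under an all-of-the-above key. In item 9 it is in the keyed option.
- **Item 10:** the keyed option has the warfarin patient taking a doctor's advice "regarding treatment with a newer anticoagulant, so as there is no need for frequent blood tests".

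Study Design has patients complete a short quiz before allocation in the Greek prepilot and says the core sample follows the same process. Intervention Cohorts again allocates Greek patients who choose to complete the quiz. Neither section says that this is the Textbox 2 quiz or that it is given again afterwards. The article does not say whether items are shown together, shown singly or read aloud. Translation for the three countries is still to come.

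**The concern.** A knowledge item should be answerable only by someone who has the knowledge. Here a patient who lacks the fact can pick up part of it from the rest of the form. Item 10's key contradicts the word 'always' in item 5 and so points to false. Stroke recurs in four consecutive items after item 4, while none of item 4's wrong options reappears in any later item.

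Only patients who do not know the fact can gain from a cue. If the VP teaches these facts better than usual information, more of those patients are in the control arm. Similar cue use in both arms then lifts control scores more and narrows the measured difference. Stroke awareness is one of the gaps the Discussion names ("patients do not identify the possibility of stroke as an acute complication of AF"), so losing sensitivity there is unwelcome. The one stated analysis of the prepilot answers ("To assess the results from the prepilot evaluation questionnaires, the Welch" *t* test) is a between-arm comparison, which would not by itself show which item leaks.

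**Working it through.** The article gives no total score, effect size, SD or power, so there is no stated figure to reproduce. Everything below follows from the scoring rule and from declared assumptions.

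**Points at stake.** There are nine items with 4 options and one with 2.

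- Maximum score = 9 × 4 + 2 = 38.
- Items 4 and 5 carry 4 + 2 = 6 points, and 6/38 = 15.8%.
- Blind guessing yields 4 × 1/4 + 2 × 1/2 = 2 of those points.
- Cueing therefore adds at most 6 − 2 = 4 points, and 4/38 = 10.5%.

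**Model (assumption).** Let k be the share of an arm that knows the fact, m the number of options, and c the share of non-knowers who use the cue. The other non-knowers guess.

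- P(correct) = k + (1 − k)[c + (1 − c)/m]
- Expected points = m × P = 1 + (m − 1)[k + c(1 − k)]
- With the same c in both arms, the between-arm difference on the item = (m − 1)(k_VP − k_control)(1 − c)

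The item's contribution therefore shrinks by the factor 1 − c.

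**Share of the total effect.** Assume the same knowledge gain d on all ten items.

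- Total without cueing = (9 × 3 + 1 × 1)d = 28d.
- Items 4 and 5 contribute (3 + 1)d = 4d, and 4/28 = 14.3%.
- Loss of total effect = c × 4/28.

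| c | Loss, both items | Loss, item 4 alone (c × 3/28) | Loss, item 5 alone (c × 1/28) |
|---|---|---|---|
| 0.25 | 3.6% | 2.7% | 0.9% |
| 0.5 | 7.1% | 5.4% | 1.8% |
| 1 | 14.3% | 10.7% | 3.6% |

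The near-explicit cue sits on the item with little weight. The heavier item has only an indirect cue, so a high c is less plausible there.

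**In points, for one assumed gap.** Suppose 80% of VP patients and 40% of controls know each fact. Items 4 and 5 then yield 0.4 × 4 = 1.6 points of difference with no cueing, and 1.2, 0.8 and 0.4 points at c = 0.25, 0.5 and 0.75. If the same gap held on every item, the total difference would be 0.4 × 28 = 11.2 points, of which 1.6 is again 14.3%.

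**In power, as an illustration only.** Take an assumed true difference of 0.3 SD, a two-sided 5% test and 175 per arm, with the SD held fixed. None of these figures is in the article. Power is 80.1% without cueing, 77.2% at c = 0.25, 74.1% at c = 0.5 and 67.2% at c = 1.

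**Direction.** If cue use differs by arm, the difference on an item is (m − 1)[(k_VP − k_control) + c_VP(1 − k_VP) − c_control(1 − k_control)]. The bias is towards zero only while the cue term for the VP arm stays below that for control. Equal cue use together with a VP benefit guarantees this.

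**The case against.** The strongest reply concerns order. Every cue comes after items 4 and 5, so a patient who answers in the printed sequence and cannot return gains nothing. Harm requires looking ahead, going back or retaking the quiz. The article is silent on presentation, and a condensed article may fairly leave that to the full protocol. The retake route needs the pre-allocation quiz to be this quiz and to be repeated, which is not stated. All of this stands and makes the point conditional.

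The item 4 cue is also weak. No later item ranks stroke above other complications, and two of the four mentions are in wrong options. A patient who believes all anticoagulants need blood tests may reject item 10's key rather than learn from it. That stands too, and is a reason to doubt values of c near 1.

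A reader might infer that patients can collect 6 points without any education. The documents do not support that: guessing already yields 2, and the remaining 4 require every non-knower to use both cues. A reader might also infer that stroke is what the trial most wants to teach. The Discussion lists it beside not recognising one's arrhythmia as AF and not seeing AF as life-threatening, without ranking them. Awareness of complications is one of three scenario criteria, the scenario is not yet chosen, and item 5 is not about stroke.

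Finally, Limitations already admits that the questionnaire is unvalidated. That admission concerns validation and coverage. It does not address cueing between items, which lies in the printed wording and which no analysis can remove.

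**Conclusion.** The point holds as a minor one. Item 10's key nearly answers item 5, and items 6 to 9 point indirectly to the answer to item 4. At stake are 6 of 38 points, at most 4 of them beyond guessing. Three conditions are needed for harm: patients can see later items before fixing their answers or take the same quiz again; non-knowers in the two arms use the cues to a similar degree; and the VP improves knowledge on these items. Given those and an equal gain across items, the total effect loses about 7% if half of non-knowers use the cues and at most about 14%. If the VP's gain were concentrated on these two items, the share would be larger; if it lay elsewhere, smaller. The knowledge shares and cue-use rates are assumptions with no source in the article. With similar cue use the bias is towards zero, so it would hide benefit rather than create it.

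**What to change.** Before the instrument is translated:

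1. Drop "so as there is no need for frequent blood tests" from item 10's keyed option. The rest of the option still stands as the correct answer, and the cue to item 5 goes.
2. Present items one at a time in the printed order, on screen or read aloud, with no going back.
3. Where the same quiz is given twice, step 2 is not enough. In that case also remove the mentions of stroke from the wrong options of items 6 and 7, which do not need them. Leave item 9's key alone: replacing stroke there with a phrase such as the complication the drug is given for would make the key nearly tautological. Accept a residual indirect cue from items 8 and 9.
4. Once the Greek prepilot has been run, and before multicentre recruitment, tabulate percent correct per item by arm to find leaking items or items nearly everyone gets right. This is a suggestion for using the prepilot, not a charge that the article omits it.

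The cost is one trimmed option, a display or reading instruction, possibly two reworded wrong options, and a small table. The one drawback is that prepilot total scores are not directly comparable with later ones if items are changed after the prepilot. Making steps 1 to 3 before it starts keeps that to a minimum.

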**5. Treatment with oral anticoagulants always mandates frequent blood tests:**
TrueFalse*

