### Limitations

The study’s core limitation lies with the knowledge retention questionnaire. This is not a validated instrument. While we were aware of a formal validated instrument (the Jessa Atrial fibrillation Knowledge Questionnaire [40]), the knowledge spectrum that it covers is far wider than what our VP vignette may cover. Given that verbal and printed conventional information covers all relevant material, while our VP may cover specific critical topics related to AF, using a wide instrument such as the Jessa Atrial fibrillation Knowledge Questionnaire would run the risk to evaluate knowledge retention gaps that the VP vignette cannot cover. While a counterargument can be made that we are thus narrowing the evaluation scope to the strong points of our VP resource, the concise focus of the VP vignette is itself an argument for implementing it as a more effective educational tool in personalized and focused endeavors for patient empowerment. As a follow through too, we aim to address the second weakness of our study, which is the lack of a qualitative exploration about the acceptance of patients regarding the electronic medium of mobile devices and the modality of VPs in comparison to other existing modalities such as video demonstration or even gamified virtual environments.

Even given these limitations, however, this study can provide evidence for the comparatively better efficacy of the VP modality in mobile media for impactful and effective information for and empowerment of patients with AF. This study would be the first evidence-based step to initiate this process toward better informing and subsequent empowerment of patients with regard to the management of their disease.

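### Every quiz statement containing 'always' is false under the key, and one option in item 6 contradicts its stem; this can trim the measurable difference by at most 7 to 10%

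*Protocol article*

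**What the plan says.** The Evaluation Instruments section of the protocol article states: "For educational efficacy, a multiple-choice questionnaire (MCQ) for knowledge retention will be used". Under Study Design, efficacy is one of the primary outcomes, so this quiz carries a primary comparison. The ten items and their key are printed in full in Textbox 2. Nine items have four choices and item 5 has two.

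Scoring is by "allocating a numerical score equal to the number of choices in the MCQ to weigh each response for randomly selecting the correct question". Each four-choice item is therefore worth 4 points and item 5 is worth 2. The weights are thus tied to the chance of guessing right.

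The word 'always' occurs in four statements:
- **Item 5 (stem):** "Treatment with oral anticoagulants always mandates frequent blood tests". Keyed False.
- **Item 6:** the option that every such patient requires curative treatment. Not keyed.
- **Item 7:** the option that the anticoagulant is stopped after three months. Not keyed.
- **Item 10:** "Always has good anticoagulation control (INR within the desired range) if he/she receives his medication in a fixed dose". Not keyed.

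No keyed answer contains the word. In item 6 the stem describes a patient who visits a cardiologist, and one option says that seeing a doctor is unnecessary.

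The Limitations section says of the questionnaire, "This is not a validated instrument", and discusses its narrow scope. It does not mention wording cues.

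**The concern.** A multiple-choice item measures knowledge only so far as a respondent without the knowledge cannot find the answer another way. Here one word marks a false statement four times out of four. A patient who distrusts absolutes gets item 5 right and removes one wrong option from each of items 6, 7 and 10. The item 6 option that clashes with its stem can be removed in the same way.

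The weighting rule makes each item worth one expected point to a blind guesser, which requires all options to be equally likely. That fails for these four items if the wording is used. Patients who do not know the content then start from a higher score, so the same gain in knowledge yields a smaller difference in points.

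**Working it through.** The article gives no effect size, SD, significance level or power, so there is no planned figure to reproduce. Intervention Cohorts says only that "sufficient sample sizes for control and intervention groups will be ensured so as to use the Welch" *t* test. The chance scores below follow from the printed items and scoring rule. The sample sizes rest on assumptions.

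**Maximum score.** 9 × 4 + 1 × 2 = 38. Items 5, 6, 7 and 10 carry 2 + 4 + 4 + 4 = 14.

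**Expected score from guessing** (sum of points × probability of guessing right):
- Blind guessing: 9 × 4 × 1/4 + 2 × 1/2 = 10.
- Rejecting 'always': the six other items give 6, item 5 gives 2, and items 6, 7 and 10 give 4 × 1/3 = 1.33 each. Total 6 + 2 + 4 = 12.0.
- Also striking the contradictory option: item 6 gives 4 × 1/2 = 2. Total 6 + 2 + 2 + 2 × 1.33 = 12.67.

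**Room above chance.**

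| Wording used | Whole quiz | Loss | Four items | Loss |
|---|---|---|---|---|
| None | 38 − 10 = 28 | – | 14 − 4 = 10 | – |
| 'Always' | 38 − 12 = 26 | 7.1% | 14 − 6 = 8 | 20% |
| 'Always' and item 6 option | 38 − 12.67 = 25.33 | 9.5% | 14 − 6.67 = 7.33 | 27% |

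For 'always' alone, if 25%, 50% or 75% of guessers use it, the whole-quiz loss is 1.8%, 3.6% or 5.4%.

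**Sample size.** Assume that a patient knows each answer with probability k and otherwise guesses, so P(correct) = k + (1 − k)g, where g is the guessing probability. Items are taken as independent, so the variance is the sum of points² × P × (1 − P). Take k = 0.5 in control and 0.6 in the virtual patient arm, two-sided alpha 0.05 and 80% power. All of these are assumptions.

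Without the cue, k = 0.5 gives P = 0.625 for four-choice items and 0.75 for item 5. The variance is 9 × 16 × 0.625 × 0.375 + 4 × 0.75 × 0.25 = 34.50. At k = 0.6 it is 30.88. The SD is √((34.50 + 30.88)/2) = 5.72, and the difference is 0.1 × 28 = 2.8.

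| Wording used by every guesser | Difference | SD | Standardised effect | n per arm |
|---|---|---|---|---|
| None | 2.80 | 5.72 | 0.49 | 66 |
| 'Always' | 2.60 | 5.60 | 0.46 | 73 (+11%) |
| 'Always' and item 6 option | 2.53 | 5.55 | 0.46 | 76 (+15%) |

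For control knowledge of 0.3 to 0.7 with the same gain of 0.1, the increase is 10 to 13% for 'always' alone and 14 to 17% with the item 6 option. At k = 0.5 versus 0.6 with half of guessers using the wording, it is about 6 to 7%. If patients also differ in knowledge (an added between-patient SD of 0.15 of the room above chance), the 'always' figure falls to about 8% (101 to 109 per arm).

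**The case against.** **The effect is small and conditional.** All of this depends on patients using the cue, and nothing in the article shows that they would. A patient whose own anticoagulant needs regular testing could well answer True to item 5. In that item 'always' is also part of the content: the Introduction says that vitamin K antagonists need coagulation monitoring and the newer agents do not, so the word is what makes the statement false. This stands. The figures are upper bounds, and it cannot be claimed that untaught patients do score higher.

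**The authors already concede an unvalidated instrument.** They do, as the study's core limitation. That tells the reader the quiz is untested; it does not identify this cue, which can be removed while the items can still be edited.

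**It does not bias the trial towards the intervention.** This stands in full. Both arms answer the same quiz, so the wording can only dilute the contrast. Allocation that is not random at two of the three sites is a far larger matter.

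**Further readings that the documents do not support.** A reader might infer that cautious wording is itself a giveaway, because the keyed options in items 6 and 10 are tentative. But item 6 has a hedged wrong option, item 10 has a wrong option opening with the same verb as the keyed one, and the key to item 7 is categorical. A reader might also infer that the cue carries into every language version. No translation is shown, and bilingual evaluation of the translation is planned, so this cannot be checked.

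**Conclusion.** The point holds as a minor item-writing flaw in a primary outcome measure. The count of four false 'always' statements, the contradictory option in item 6, and the chance scores of 10, 12.0 and 12.7 of 38 are all verifiable from Textbox 2. The loss of room above chance is at most 7% for 'always' alone and 10% with the item 6 option, and it shrinks in proportion to the unknown share of guessers who use the wording.

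The 11 to 15% sample-size equivalent applies only if every guesser uses it, under the assumed knowledge shares, independent items, alpha and power. A reader might square the ratio of room and arrive at 16 to 22% (1/(26/28)² = 1.16; 1/(25.33/28)² = 1.22). That holds the SD fixed, whereas under this model the SD falls as well, from 5.72 to 5.60 or 5.55, so the higher figure is not supported.

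**What to change.** Edit the four items before the quiz is translated, and leave the clinical content of the key unchanged.

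- **Items 7 and 10:** remove 'always' from the wrong options. They remain wrong under the present key without it.
- **Items 5 and 6:** do not simply delete the word, because it helps make these statements false. Without it, item 5 would be true of one drug class and false of the other, and the item 6 option could become arguable. Either use 'always' in some keyed-true statements as well, so that the word no longer signals the answer, or replace each statement with one that is plainly false without it under the existing key.
- **Item 6:** replace the option that contradicts the stem with a plausible distractor.

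The cost is a short rewording exercise and a check by the clinical experts that each key still holds. The downside is that scores are no longer exactly comparable with any prepilot data collected on the old wording.
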